### Description and diagram of trial design

The town of Uvira was divided into sixteen clusters stratified into two groups due to the project funding structure and planned works sequence: South (*n* = 6, areas primarily served by the existing tank) and North (*n* = 10, areas primarily served by the new tank) (Fig. 1). The existing and new tank will both eventually belong to the same water supply network and contribute to improving water service across all clusters. The primary criteria used to define clusters were the total length of pipes to be rehabilitated or installed and the number of new community taps; the secondary criteria included considerations such as alignment with existing administrative zones and natural features such as rivers. Key characteristics of the study clusters are presented in Table 1.

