**Fig. 1 Fig1:**
[figure not shown]
Map of Uvira with the definition of clusters and groups: South (blue, *n* = 6) and North (pink, *n* = 10)

**Table 1 Tab1:** Key cluster characteristics

Cluster #	Estimated population (March 2018)	Area [km^2^]	*Mean # suspected cholera cases per month	*Mean monthly incidence per 1000	Existing pipe length [m]	Pipe length to rehabilitate [m]	Length of new pipes to install [m]	# existing household connections	# provisionally planned new household connections	Number of planned new community taps	Allocation sequence
1	4291	2.02	1.9	0.4	2152	57	2628	16	66	6	15
2	4990	0.76	6.0	1.2	1578	1658	1792	89	25	3	16
3	11,183	0.87	6.4	0.6	5574	1266	1864	171	25	7	10
4	7328	1.02	5.4	0.7	2347	0	3398	25	100	5	12
5	13,649	1.27	4.4	0.3	2786	797	4177	19	205	4	9
6	8389	0.48	5.8	0.7	1730	499	2328	43	82	6	13
7	7480	0.37	2.0	0.3	4525	367	1065	152	26	2	8
8	15,455	0.43	4.8	0.3	2961	1097	1793	199	25	5	7
9	3994	0.36	9.4	2.4	3848	189	2446	183	25	8	11
10	14,175	0.59	7.1	0.5	8901	692	1520	525	25	7	1
11	56,106	1.70	14.5	0.3	8775	1599	2401	633	254	16	5
12	12,462	0.99	3.0	0.2	2292	1455	1844	22	193	1	14
13	50,764	2.75	10.4	0.2	17,781	1666	1266	1384	24	11	4
14	16,175	0.55	6.7	0.4	907	0	2549	35	220	5	3
15	15,183	0.81	7.2	0.4	4091	135	2420	161	62	9	2
16	19,338	1.98	10.6	0.6	1788	2061	2874	28	318	20	6
**Mean**	**16,310**	1.06	6.6	0.4**	72,033	13,538	36,363	3685	1675	7.2	–
Minimum	3994	0.36	1.9	0.2	907	0	1065	16	25	1	–
Maximum	56,106	2.75	14.5	2.4	17,781	2061	4177	1384	318	20	–

*Based on CTC admissions between January 1, 2009, and March 31, 2018, and population in March 2018

**Mean weighted by cluster population size

Within each group (South and North), clusters were randomised to different initiation periods by the research team using a random number generator, with the intervention delivered to the South clusters first. The intervention interval—or “step”—during which time a given cluster receives the intervention was planned to be 4 weeks; this interval was extended to up to 8 weeks for the installation of new household connections to the water supply network (Fig. 2)—the reasons are discussed below.

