### Analysis plan

The SW-CRT and ITS analyses are detailed hereafter.

A generalised estimating equations (GEE) Poisson regression for rates will be used with robust standard errors. An indicator of water service quality will be included, which may integrate users’ distance to taps, hours of water availability, or volumes distributed, for example, to reflect improvements brought by the intervention in terms of water service. To account for seasonality a harmonic term for time (in months) will be included. This analysis accounts for correlations between individuals within clusters, as well as repeated measures of the same clusters over time. A small sample correction will be considered to adjust for the small number of clusters [57]. Note that data collected during the transition period for each cluster will not contribute to the analysis.

Since the intervention takes place over less than 2 years, the seasonal pattern of cholera infection may not be estimated correctly using only data from the trial period. A sensitivity analysis will be carried out using historical data from the cholera treatment centre which is available from 2009 to the start of the trial. The model will be re-fitted using the same covariates, with all historical data considered non-intervention time. We will also consider the inclusion of a treatment by time interaction term in the GEE model as part of further sensitivity analyses linked to seasonality.

An intention-to-treat analysis will be carried out for the main analysis. The above models will be repeated with the other primary outcome: rate of confirmed cholera cases per 1000 residents.

Randomisation may be particularly challenging to ensure given the nature of the intervention. If the randomisation scheme is not adhered to, balance between arms cannot be assumed. In this case, relevant confounders which may be associated with intervention allocation and outcome will be included in the main analysis, as they would be in non-randomised settings. These may include patient’s age and sex, and factors related to their household location such as water service quality and distance from the cholera treatment centre.

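### The South-before-North order is fixed, not randomised, yet the main model names no group or cluster term and adjusts for confounders only if randomisation is breached

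*Protocol article*

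**What the plan says.** Under Description and diagram of trial design, the town is "divided into sixteen clusters stratified into two groups due to the project funding structure and planned works sequence". The text below Fig. 1 and Table 1 explains how the sequence was drawn: "Within each group (South and North), clusters were randomised to different initiation periods by the research team using a random number generator". That draw did not cover which of the two groups starts, because this was settled beforehand: "with the intervention delivered to the South clusters first".

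The Analysis plan gives the main model: "A generalised estimating equations (GEE) Poisson regression for rates will be used with robust standard errors". It adds an indicator of water service quality and a seasonal term: "To account for seasonality a harmonic term for time (in months) will be included". No South/North term, cluster intercept or group-specific time term is named, and the working correlation is not given. A small-sample correction is to be considered. Confounders enter the main analysis only in the event that the randomisation scheme is not adhered to, and the examples given do not include the South/North group.

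Under Research-specific challenges and limitations, the mid-trial start of the new tank, the flexible steps and the heterogeneity of the clusters are to be handled by considering potential confounders. The groups are not named there either.

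**The concern.** The adjustment rule has the wrong trigger. It treats balance as secured whenever the sequence is followed. But a sequence followed to the letter still treats every South cluster before any North cluster, for reasons of funding and works planning. Randomisation protects only the order within each group.

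Early intervention time is then always South and late control time is always North. If the groups differ in underlying incidence, a model that compares between clusters counts part of that difference as intervention effect. Here the low-incidence group goes first, so the error would look like benefit. The gap between the groups (40%) is larger than the 25% reduction that the trial is sized to detect.

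**Working it through.** **Inputs.** Population, mean monthly suspected cases and allocation sequence come from Table 1, whose rates are "Based on CTC admissions between January 1, 2009, and March 31, 2018, and population in March 2018". The map is not shown, so membership is inferred: six South clusters go first, hence sequence 1–6 (clusters 10, 11, 13–16) is South and 7–16 (clusters 1–9, 12) is North.

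**The plan's own figures.**
- Overall rate: 105.6 cases per month / 260,962 people = 0.405 per 1000. This reproduces the stated 0.4.
- Detectable difference: the Hussey-Hughes variance with 16 one-cluster steps, 17 periods, 16,000 per cluster, ICC 0.3, 80% power and two-sided 5% gives 0.093 per 1000. This rounds to the stated 0.1, and 0.1/0.4 = 25%.

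**Rates by group.**
- South: 7.1 + 14.5 + 10.4 + 6.7 + 7.2 + 10.6 = 56.5 cases per month; 56.5 / 171,741 = 0.329 per 1000.
- North: 105.6 − 56.5 = 49.1; 49.1 / 89,221 = 0.550 per 1000.
- Ratio: 0.329 / 0.550 = 0.60. South holds 171,741 / 260,962 = 66% of the population.
- Without cluster 9 (9.4 cases, 3,994 people): North 39.7 / 85,227 = 0.466, ratio 0.71.

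**How exposure lines up with group.** Assume one cluster starts per month for 16 months, with one transition month excluded and no extra months before or after. The cluster in position k then gives k − 1 control months and 16 − k intervention months.
- South (k = 1–6): 0+1+2+3+4+5 = 15 control and 15+14+13+12+11+10 = 75 intervention months.
- North (k = 7–16): 6+7+…+15 = 105 control and 9+8+…+0 = 45 intervention months.

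**Null fits.** Expected counts were set to the Table 1 cluster rates with no intervention effect and an assumed seasonal log-amplitude of 0.5. The model was a Poisson GEE with a 0/1 intervention term, one annual sine/cosine pair and a log-population offset. The true rate ratio is 1.00. Results below are for a one-month transition; two months changes them little.

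| Months before / after roll-out | Independence, no group term | Independence, South/North term | Exchangeable, no group term |
|---|---|---|---|
| 0 / 0 | 0.78 | 0.96 | 1.02 |
| 4 / 2 | 0.82 | 0.95 | 1.00 |
| 6 / 12 | 0.86 | 0.96 | 0.99 |
| 12 / 12 | 0.91 | 0.99 | 1.00 |

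Over all the fits made, the ranges are:
- Independence, no group term: about 0.75–0.91.
- Exchangeable, no group term: about 0.94–1.04.
- South/North term alone, independence: about 0.92–0.99.
- Cluster fixed intercepts: 1.00 in every scenario. With constant rates and a shared season, that model fits the expected counts exactly.
- About 110 historical months added as control time, independence: 0.91 with no post-period and 0.95 with 12 months.

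**Rejection of a true null (nominal 5%, robust SE, 200 simulations per scenario).** Independence without a group term: 27–57%; with it: 7–14%. Exchangeable: 9–12% with or without the term.

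**Different trends.** If only the North rate falls by 2% a month (assumed), a South/North main effect still leaves about 0.83–0.91, whichever working correlation is used.

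**The case against.** The strongest reply is that the large figures all need working independence, which the article does not state. It says that the GEE accounts for correlation within clusters and for repeated measures over time. This does not fix the structure, since robust errors under independence would also satisfy it, but it gives no ground to presume independence. Under exchangeable correlation the comparison is mostly within cluster and the missing group term hardly matters. This stands, and it makes the size conditional.

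Four further points limit the finding:
- A reader might put all the excess false positives down to the South-North contrast. The documents do not support that. A small-sample correction is under consideration, and under independence without a group term a bias-reduced robust error with 14 degrees of freedom cut null rejection from 24–30% to 5–10%. Part of the excess is thus the usual error of an uncorrected sandwich with 16 clusters. The correction does not move the biased point estimate.
- A reader might say that the plan ignores the groups. That is too strong, because the limitations section does promise to consider confounders for the tank timing and the heterogeneity in Table 1. The promise names no group, however, and does not lift the conditional rule in the Analysis plan.
- The refit with data from 2009 shrinks the bias, and the interrupted time series does not use the staggered order. Both are supporting analyses, and the latter detects only reductions of 65% to 75%.
- Table 1 rates are historical, and cluster 9 drives part of the gap. Without it, the 12/12 independence result is 0.93.

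Models with month effects but no group or cluster term do much worse (0.57), but the plan does not propose such a model, so that figure does not count against it.

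**Conclusion.** The point holds in conditional form. By design the South-North order is not randomised, and the stated rule leaves it unadjusted exactly when the trial runs as planned. The documents do not show that the primary estimate will be biased. They show that it could be, towards benefit, depending on an unstated choice: a spurious reduction of roughly 9% to 25% under working independence, and little or none under exchangeable correlation.

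These sizes rest on Table 1 rates carrying into the trial period, one cluster starting per month, a 0/1 term in place of the planned service-quality indicator, and group membership read from the sequence. The design fact and the misplaced trigger rest on none of these assumptions.

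**What to change.** Include cluster fixed intercepts in the primary model for both outcomes. They absorb the South/North level difference and make the result under constant rates independent of the working correlation. A South/North term alone is weaker. State that this adjustment applies whether or not the randomisation sequence is followed, and keep the existing conditional rule for further confounders.

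Two additions are useful but optional:
- A permutation test that re-orders clusters within South (6!) and within North (10!), which mirrors the randomisation actually done.
- Group-specific calendar time as a sensitivity analysis. Cluster intercepts remove differences in level but not in trend, and the groups are served primarily by different tanks, one of which starts half-way.

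The main change costs analysis wording and almost no precision. The group-by-time sensitivity analysis has a wider confidence interval (minimum detectable reduction about 32% against 24% under Poisson variation alone).

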**Fig. 2 Fig2:**
[figure not shown]
Trial diagram, inspired by [46]

### Participants

The population of interest is all inhabitants of Uvira, assuming that all Uvira inhabitants affected by severe diarrhoeal disease or cholera will eventually seek care or be referred to the CTC. All patients admitted to the CTC with suspected cholera are eligible for participation in the study and collection of a rectal swab for cholera confirmation (Fig. 2). No restriction is placed on patient age.

Following approval by the Ministry of Health for DRC, the CTC Coordinator can extract and share anonymised patient information as recorded in the CTC registry, including age, sex, address, dates and length of stay, and antibiotic treatment if any. All information that is extracted and included in this study protocol is anonymised with no personal identifiers included. Aggregated census data provided by municipal authorities will be used to estimate the population size for each cluster.

### Outcomes

Two primary outcomes will be used to assess the effectiveness of the intervention: (1) the monthly incidence of suspected cholera cases, as measured by the number of CTC admissions attributed to each cluster; (2) the monthly incidence of confirmed cholera cases, based on rapid detection test (RDT) results for eligible, consenting patients.

### Trial data collection

Information will be collected to characterise the water supply intervention as well as to monitor health outcomes.

Monitoring tools were developed to record progress of construction works on the water supply network. For each new community tap and each household connection in this project, a form will be completed that includes information on location (address, cluster number, GPS coordinates), owner (for household connections), type of connection (new or rehabilitated), and date of works completion. For household connections, the date of works completion will correspond to the date of actual service availability for the users. For community taps, the date of service availability may be different from that of works completion and will be recorded by management committee agents in the registers used to monitor water use.

Additionally, in order to further assess the intensity of the intervention, we will use the total volume of water distributed (m^3^/day) as measured at the exit of the pumping station and the total volume of water billed to users (m^3^/month per cluster), depending on data availability.

In parallel to the intervention, data will be collected at the CTC on an continuous basis, with all admissions and corresponding patient addresses recorded to allow assignment to study clusters, and rectal swabs collected from eligible, consenting patients for cholera confirmation via Crystal VC RDTs (Span Diagnostics, Surat, India) on alkaline peptone water enrichments, as described elsewhere [21]. The sensitivity and specificity of RDTs on enriched rectal swabs was estimated to be 92% and 91%, respectively [56]. Enriched samples testing positive via RDTs may be preserved on filter paper for *Vibrio cholerae* isolation and characterisation at a partner laboratory.

### Blinding

Blinding of participants to the intervention is not possible due to the nature of the intervention: hydraulic construction works are visible and affect water services where they are implemented. However, whether an individual lives in a control or intervention cluster at a given point in time is unlikely to affect care-seeking behaviour for acute diarrhoea and cholera confirmation remains an objective outcome, independent of a patient’s cluster status.

### Analysis plan

The SW-CRT and ITS analyses are detailed hereafter.

A generalised estimating equations (GEE) Poisson regression for rates will be used with robust standard errors. An indicator of water service quality will be included, which may integrate users’ distance to taps, hours of water availability, or volumes distributed, for example, to reflect improvements brought by the intervention in terms of water service. To account for seasonality a harmonic term for time (in months) will be included. This analysis accounts for correlations between individuals within clusters, as well as repeated measures of the same clusters over time. A small sample correction will be considered to adjust for the small number of clusters [57]. Note that data collected during the transition period for each cluster will not contribute to the analysis.

Since the intervention takes place over less than 2 years, the seasonal pattern of cholera infection may not be estimated correctly using only data from the trial period. A sensitivity analysis will be carried out using historical data from the cholera treatment centre which is available from 2009 to the start of the trial. The model will be re-fitted using the same covariates, with all historical data considered non-intervention time. We will also consider the inclusion of a treatment by time interaction term in the GEE model as part of further sensitivity analyses linked to seasonality.

An intention-to-treat analysis will be carried out for the main analysis. The above models will be repeated with the other primary outcome: rate of confirmed cholera cases per 1000 residents.

Randomisation may be particularly challenging to ensure given the nature of the intervention. If the randomisation scheme is not adhered to, balance between arms cannot be assumed. In this case, relevant confounders which may be associated with intervention allocation and outcome will be included in the main analysis, as they would be in non-randomised settings. These may include patient’s age and sex, and factors related to their household location such as water service quality and distance from the cholera treatment centre.

As a complement to the main stepped-wedge analysis, an additional analysis will be carried out which makes fewer assumptions about the structure of the intervention. An interrupted time series analysis will be fitted using historical data, with a fixed starting point for the intervention rather than staggered starting points as assumed in the analysis above. Data collected throughout the intervention until completion of the works in the last cluster will be excluded from the analysis. We intend to continue data collection for at least 12 months after completion of the intervention to allow comparison of suspected and confirmed cholera incidence before and after water service improvements.

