### Research-specific challenges and limitations

From a research standpoint, the fact that the new tank, which is expected to improve service quality in all clusters, will be put into service half-way through cluster-level improvements (Fig. 2) and the flexible step duration (and o verlap between steps) to allow prolonged installation of new household connections—another pragmatic choice required to adapt to the context—both represent deviations from a standard SW-CRT roll-out. Likewise, the heterogeneity in cluster characteristics (Table 1), due to local constraints, is large for a SW-CRT. These aspects will be accounted for in the stepped-wedge analysis by considering potential confounders. An ITS analysis will also be conducted, which does not depend in any way on the intervention structure and implementation.

Spill-over effects could also potentially undermine the study design if inhabitants of a control cluster are able to use an improved “intervention” water service in a neighbouring cluster; for example, if a new private connection is used by multiple households. While household surveys may provide insights into the actual use of water services, we will not be able to systematically assess intervention compliance over the entire city. An intention-to-treat approach will therefore be used in the analysis and a sensitivity analysis will be performed to assess the influence of excluding participants who live within spatial buffers of different widths along the clusters’ borders. Given the predominance of within-household cholera transmission over infection from environmental sources [41, 61], we expect spill-over effects, if any, to remain of limited magnitude.

The reliance on clinical surveillance to assess cholera incidence is another limitation of this evaluation, as it may be influenced by healthcare-seeking behaviour. Although we will not be able to quantify CTC attendance rates for diarrhoeal disease symptoms across Uvira, we will seek to collect information on care habits during the household survey and critically review assumptions related to healthcare use for diarrhoeal diseases. The confirmation of cholera cases by RDTs rather than by culture or molecular methods (PCR) also responds to the need for pragmatic research approaches, as RDTs were identified as the only confirmation method that could be reliably used in the Uvira context considering available resources and laboratory capacity at the time this study started.

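### The main model includes a post-intervention water-service indicator whose role is undefined; whether covariate or exposure, it does not give the intention-to-treat effect the article states

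*Protocol article*

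**What the plan says.** The Analysis plan section of the protocol article describes a GEE Poisson model for rates with robust standard errors. It names two kinds of term: a harmonic term for season, and a service variable. On the latter it says: "An indicator of water service quality will be included". Tap distance, supply hours and distributed volume are offered as possible components. The stated purpose is "to reflect improvements brought by the intervention in terms of water service". The inclusion is unconditional, and only the composition of the indicator is left open.

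The same section says: "An intention-to-treat analysis will be carried out for the main analysis". Under Research-specific challenges and limitations the article adds: "An intention-to-treat approach will therefore be used in the analysis". The reason given there is that compliance cannot be assessed systematically across the whole city.

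A treatment term is not listed in the model description, but it is implied elsewhere. One sensitivity analysis reads: "We will also consider the inclusion of a treatment by time interaction term in the GEE model". Another reads: "The model will be re-fitted using the same covariates, with all historical data considered non-intervention time". The description of the interrupted time series also says that the main analysis assumes staggered starts.

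Finally, if the allocation order is not followed, possible added confounders include age, sex and "factors related to their household location such as water service quality".

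**The concern.** Taps, production capacity, storage and network loops are what the works deliver (Intervention section). Tap distance, hours of supply and volumes are how that delivery would show. The article also cites earlier work in Uvira linking service interruptions to diarrhoeal disease (Administrative and technical challenges). On the article's own account, then, the indicator lies between the intervention and the outcome.

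An intention-to-treat effect in a stepped-wedge trial compares cluster-periods by their randomised status, whatever service was actually received. A model that holds received service fixed, or that uses it as the exposure, answers a different question. Both primary outcomes use this model, so the stake is what the trial's main result estimates. On one reading a real benefit could be shrunk towards no effect. On the other, the protection of randomisation is given up while the intention-to-treat label stays.

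**Working it through.** **Step 1. The plan's own figure.** Inputs from Sample size: rate 0.4 per 1000 per month, ICC 0.3, 16,000 people per cluster, 80% power, 5% significance (taken as two-sided, since a decrease or an increase is quoted). Layout: 16 clusters, one per step, hence 17 periods.

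The Hussey-Hughes variance is Iσ²(σ² + Tτ²) / [(IU − W)σ² + (U² + ITU − TW − IV)τ²], with:
- I = 16, T = 17, U = 136, W = V = 1496
- p(1 − p) = 0.0004 × 0.9996 = 0.00039984
- σ² = 0.00039984 / 16,000 = 2.499 × 10⁻⁸
- τ² = (0.3/0.7) × 0.00039984 = 1.714 × 10⁻⁴

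The standard error is 3.33 × 10⁻⁵. Multiplied by 2.80 (1.96 + 0.84), it gives 0.0934 per 1000, or 23.3%. This rounds to the stated 0.1 per 1000 (25%). The formula has no service covariate, so the stated detectable difference belongs to the contrast by schedule alone.

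**Step 2. Indicator as covariate, closed form.** Assume a true rate ratio of 0.75, 80% power without the indicator, and a share q of the log effect carried by measured service. The article gives no value for q. Adjusted rate ratio = 0.75^(1−q). Power = Φ(2.80(1−q) − 1.96), with the standard error held fixed.

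| q | Adjusted rate ratio | Power |
|---|---|---|
| 25% | 0.75^0.75 = 0.81 | Φ(0.14) = 56% |
| 50% | 0.75^0.50 = 0.87 | Φ(−0.56) = 29% |
| 80% | 0.75^0.20 = 0.94 | Φ(−1.40) = 8% |

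**Step 3. Simulation of both readings.** Populations, case rates and allocation order come from Table 1. The following are assumptions, not in the article: 24 months, a two-month transition dropped, harmonic season, cluster fixed effects in place of GEE, overdispersion, a true rate ratio of 0.75, an indicator that rises by one unit at the intervention with noise SD 0.3 or 1.0, and 150 runs per case. Each pair gives the result for noise SD 0.3 / 1.0.

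| Share mediated | Schedule only | Schedule, adjusted for indicator | Indicator only (per unit) |
|---|---|---|---|
| 0 | 0.75 / 0.74 | 0.75 / 0.75 | 0.82 / 0.95 |
| 50% | 0.76 / 0.75 | 0.89 / 0.86 | 0.79 / 0.85 |
| 80% | 0.76 / 0.75 | 0.94 / 0.94 | 0.77 / 0.79 |
| 100% | 0.76 / 0.75 | 1.01 / 1.00 | 0.76 / 0.75 |

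The schedule-only model recovers the total effect in every row. With the indicator added, the schedule coefficient is attenuated as q grows. When the indicator follows the rollout closely (noise SD 0.3), the spread of the log rate ratio also rises, from 0.08–0.10 to 0.13–0.15, so the power figures in Step 2 are before that loss. The indicator-only coefficient adjusts nothing away, but it is a per-unit association that moves with measurement noise and mediated share. It is not the randomised contrast.

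**Step 4. What drives service received.** New household connections depend on application and a fee, and the supervising team may move them between clusters (Intervention). Affordability may limit uptake (Economic challenges). Electricity shortages are the main cause of intermittent supply, and the project does not address them (Administrative and technical challenges). None of these is randomised.

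**The case against.** The strongest defence is that the article does not say that the indicator sits beside a treatment term. Its stated purpose reads naturally as a graded exposure, and then nothing is adjusted away. A reader might infer from the model paragraph that the treatment effect will be removed from the primary result. The text does not support that as fact: it needs a separate treatment term, which is only implied elsewhere, and full removal needs full mediation. This part of the defence stands. It does not rescue the intention-to-treat label, because the graded-exposure reading also fails to give that effect.

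The direction is not certain either. Common causes of service and cholera could bias the adjusted estimate either way. Volume distributed is measured at the pumping-station exit (Trial data collection), so that component is town-wide and cannot separate clusters within a month.

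A second defence is the new tank, which is expected to improve service in all clusters and enters service half-way through the rollout. A 0/1 status then counts some improved clusters as control. The difficulty is real and the article discloses it. It calls for adequate time terms and a secondary exposure-response model, not a post-intervention variable in the intention-to-treat model.

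Third, a reader might infer that the fallback list repeats the same fault. That is not established. The list is optional and applies only if allocation is not followed. Service before the works differs widely (Table 1: 16 to 1384 existing household connections) and could be a legitimate confounder. Nor does the article show that age and sex cannot be used: the Participants section mentions census totals for cluster size and is silent on any breakdown.

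A separate analysis plan may fill in detail, but the conflict lies between statements the article itself makes.

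**Conclusion.** The concern holds in this form: the article commits the main model to a post-intervention service variable, leaves its role and metric open, does not explicitly name randomised cluster-period status as the exposure, and calls the result intention-to-treat. Neither available reading delivers that effect. Because it decides what both primary outcomes estimate, it should be settled before analysis.

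The size can be illustrated for the covariate reading only, and it rests on an assumed mediated share, a true rate ratio of 0.75 and 80% power at that value. The figures show direction and range; they do not measure bias in this trial. For the exposure reading the fault is one of kind, a non-randomised exposure-response analysis under the wrong label, and no single figure applies. The fallback list needs clarification only.

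**What to change.** - **Primary model:** name randomised cluster-period status (0/1, transition excluded) as the exposure, with time terms, and include no post-intervention service variable. The time terms should be able to absorb a town-wide change when the tank is commissioned, which a seasonal harmonic alone cannot.
- **Service indicator:** move it to a pre-specified secondary exposure-response or mediation analysis with its metric fixed and without the intention-to-treat label. This is also where the tank's effect on service in all clusters can be examined.
- **Fallback list:** restrict water service quality to values from before the works. Use age and sex only if census denominators by age and sex exist for each cluster.

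The cost is wording; no data are lost and the stated detectable difference is unchanged. One small downside should be stated: with the tank serving all clusters, the 0/1 contrast estimates the effect of the cluster-level works only.
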